### **Sample size estimation**

Assuming that 75% of individuals are virally suppressed at baseline and very conservative intraclass correlation between facilities of 0.2, we estimated that we would be able to detect a 10.7% difference between intervention and control arms with 80% power and at  $p<0.05$  if we used approximately 60 patients at each clinic at each of the 16 facilities in waves 1 and 4, for a total maximum of approximately 960 (480 in sequence 1 & 480 sequence 4) viral loads. At each facility, we sought to balance recruitment among new ART starters, individuals who were more than 30 days late (lost or late), and individuals who were in care). The reason for using a sub-cohort is that in we sought to evaluate effects in a “real world” delivery setting, but in these setting outcome ascertainment under routine conditions can be a challenge. By identifying a sub-cohort who are representative of all, but in whom additional data collection at baseline about contact information will allow more intensive outcome ascertainment at the end of the trial to ensure outcome ascertainment.

## **4.0 – Secondary Outcome – Patient Experience**

### **Trained exit client (TEC) survey data**

For TEC analysis, the measure of interest was onl

y collected in waves 2, 3, and 4. In wave 1 (first 6 months), all facilities adhered to the standard of care. This was to ensure that all waves included at least one baseline period where they were in the control state to increase power. This was an open-label trial in which HCW/ facilities and patients were unblinded to the intervention itself. However, the timing of the transition was only revealed to facilities during sensitization at time zero. Facilities were then reminded of the transition two weeks before the intervention was introduced.

#### TEC survey population

|                   | Period 1                                                          | Period 2                                                               | Period 3                                                              | Period 4                                                               | Totals per wave |
|-------------------|-------------------------------------------------------------------|------------------------------------------------------------------------|-----------------------------------------------------------------------|------------------------------------------------------------------------|-----------------|
| Wave 1            |                                                                   |                                                                        |                                                                       |                                                                        |                 |
| Wave 2            | Control
30 patients x 4
facilities =
120 patients | Intervention
30 patients x 4
facilities =
120 patients | Intervention
15 patients x 4
facilities =
60 patients | Intervention
15 patients x 4
facilities =
60 patients  | 360 patients    |
| Wave 3            | Control
15 patients x 4
facilities =
60 patients  | Control
15 patients x 4
facilities =
60 patients       | Intervention
15 patients x 4
facilities =
60 patients | Intervention
15 patients x 4
facilities =
60 patients  | 240 patients    |
| Wave 4            | Control
15 patients x 8
facilities =
120 patients | Control
15 patients x 8
facilities =
120 patients      | Control
30 patients x 8
facilities =
240 patients     | Intervention
15 patients x 8
facilities =
120 patients | 600 patients    |
| Totals per period | 300 patients                                                      | 300 patients                                                           | 360 patients                                                          | 240 patients                                                           | 1200 patients   |

#### Study Population:

TEC patients are drawn from patients who were adults over 18 years of age at time of recruitment, on or had been on treatment, with at least one clinical visit between 17th August 2019 and 17th November 2021 (which we used to define the study population) in study facilities. TEC patients were included both patients in care (who were recruited in the waiting room through systematic sampling of every kth patient where k depended on the facility size) as well as patients who had been in care but were lost to follow up (at least 30 days late for a visit) who were approached through the phone or contact through tracing in the field. The patients were drawn from facilities in waves 2, 3 and 4 during both control and intervention periods (Figure)

#### Measures:

We assessed the impact of the PCC training and mentorship intervention on patient satisfaction/ experience. The patient experience measurement was broken into several domains: 1) coordination within a care team, 2) coordination across care teams, 3) continuous familiarity with patient over time, 4) continuous proactive and responsive action between visits, 5) patient-centered communication and engagement, and 6) shared decision making and appointment arrangements.

#### Analysis

The analytic strategy for TEC will be focused on assessing the effectiveness of the PCC intervention by comparing the PCC intervention group to the control group. The unit of randomization is healthcare facility and the unit of analysis is the individual. To test the effectiveness of the

intervention, we will use a standard stepped-wedge analytic approach (Hussey & Hughes, 2007) based on a generalized linear mixed model (GLMM) where facility is included as a random effect and period is included as a fixed categorical variable to adjust for secular trends. Due to a ramp up in intervention effect, we will determine code three different groups for the intervention analysis (control, early intervention ( $\leq 6$  months), late intervention ( $> 6$  months), fit as separate categories or ordered (Hughes et al., 2015; Kenny et al., 2021)). This decision is based on contextual experience in the facilities and anticipation that there will be a lag in seeing the benefits from training, mentoring, and data feedback (e.g., the first data feedback only occurred 3 months into the intervention). Furthermore, we will explore alternative parameterizations for secular trends including linear and cubic splines. If these alternative parameterizations better describe variability in the data (as determined by standard model fit statistics such as Akaike's Information Criterion [AIC]) then the model will be updated to reflect this accordingly. Distributions and link functions used will depend on the outcome (see outcome-specific sections below for more details).

We will also include the following variables in our statistical models as they are thought to be causally related to the outcomes: age at enrollment, sex, in-care status, randomization strata (initial cluster randomization stratified by facility size and viral load coverage based on programmatic data). We will consider including the following potential confounders due to imbalance in randomization: time in care, WHO severity groups, marital status and education. We will use Fisher's exact tests, t-tests, and Wilcoxon rank-sum tests, as appropriate. Variables that exhibit some evidence of a difference between groups ( $P < 0.10$ ) will be included in the final statistical models. In the event that any of these variables have strong associations with the intervention groups but have high levels of missingness (e.g.,  $> 10\%$ ) then those variables will be excluded from the main analysis and will be further explored using sensitivity analyses (for more details see sensitivity analysis section below). We will use standard model diagnostic procedures and consider alternate specifications as needed if we face challenges with standard statistical issues such as model convergence or overfitting.

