#### *Analysis of individual questions from TEC survey*

We will analyze 12 dichotomous (yes/no) patient experience questions from the trained exit client (TEC) survey. Initially, binomial models with a log link (relative risk) or identity link (risk difference) will be used to analyze these data. However, it is well-known that models assuming a binomial distribution often fail to converge (Spiegelman, 2005), and if we find widespread convergence failure for either of the link functions then we will employ models that assume a Poisson distribution. If convergence issues still persist then we will also explore alternative modelling for random effects (e.g., GEE). Significant differences ( $P < 0.05$ ) with greater proportions of positive experiences in the PCC intervention group will support the hypothesis that the PCC intervention was more effective compared to the control. Results will be presented in terms of risk ratios (95% CI) and risk differences (95% CI). Forest plots with these estimates and 95% CIs will also be used to visually display the results. Additionally, we will present the absolute percentages to assess where the improvements any improvements are occurring (e.g., 40% to 50% vs 85% to 90%).

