## **Sensitivity analyses**

Sensitivity analyses will entail assessment of intervention effects for variables with high levels of missingness that were not included in the main analysis. We will explore the analyses including these variables without any imputation as well as imputing extreme values (e.g., all “yes” or all “no” responses missing values) to assess the degree which this influences our inferences for the intervention effectiveness. We will explore alternate specifications for the intervention variable where we assume the maximal intervention effect will be quicker (i.e., 3 months) or longer (i.e., 9 months). We will also explore whether treating period as an ordered variable and whether using visit date (as opposed to period) better describes the data.

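### In the TEC analysis, a fit statistic computed on the trial data may replace categorical period; this could raise the late-effect type I error from about 5-6% to at most about 8% under an assumed mild non-linear trend

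*Combined protocol and SAP*

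**What the plan says.** SAP section 4.0, Analysis, specifies a Hussey-Hughes mixed model with a facility random effect, in which "period is included as a fixed categorical variable to adjust for secular trends". Exposure is coded as control, early (up to 6 months) or late (beyond 6 months), "fit as separate categories or ordered".

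The same paragraph adds that "we will explore alternative parameterizations for secular trends including linear and cubic splines". It continues: "If these alternative parameterizations better describe variability in the data", as "determined by standard model fit statistics such as" AIC, "then the model will be updated to reflect this accordingly". Knots, degrees of freedom and a minimum AIC difference are not given. Nothing requires the categorical-period result to be kept or reported.

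The Sensitivity analyses part of section 4.0 separately lists period as an ordered variable and "whether using visit date (as opposed to period) better describes the data". The protocol's analysis of trained exit interviews (Analysis for Objective 2) names the Hussey-Hughes method and contains no selection step.

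**The concern.** Calendar time is the main confounder in a stepped wedge, because exposure rises with time by design. The late contrast depends heavily on how time is modelled. In the SAP's TEC table, late exposure falls in wave 2 (Periods 3 and 4) and wave 3 (Period 4), with 60 patients in each cell: 180 of 1,200, of whom 120 are in Period 4. In Period 4 every wave is on intervention, so there is no concurrent control.

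If a smoother time form replaces categorical period, the part of the trend that it cannot follow may be absorbed by the late term. AIC protects least where the departure is too small to be detected reliably but large enough to bias. The reported interval would also ignore that the form was selected. A non-linear trend is plausible: the Figure S1 legend says that Period 2 coincided with the COVID-19 emergency and was extended. The rule sits in the common TEC model, so it could give different time forms for the 12 items, the PCA scores and the sum score.

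**Working it through.** **Inputs from the SAP.** 16 facilities (waves 2, 3 and 4 with 4, 4 and 8); 15 or 30 patients per facility-period; baseline 65%; ICC 0.2; early and late terms; normal model with identity link for the scores. The 0.05 level comes from the item analysis ("Significant differences ( $P < 0.05$ ) with greater proportions of positive experiences"); sidedness is not stated, so two-sided is assumed. **Assumed:** the size and shape of the trend, in outcome SD units, and a second ICC of 0.05.

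**1. The plan's own figure.** The SAP states a 15.0-point detectable difference at 80% power. Take the Hussey-Hughes variance for a single intervention effect, 16 facilities × 4 periods, 15 per cell, total variance 0.65 × 0.35 = 0.2275 and ICC 0.2. The detectable difference is 14.68 points, so SE = 14.68 / 2.8016 = 5.24 points, and power = Φ(15.0/5.24 − 1.96) = Φ(0.90) ≈ 82%. This agrees with the SAP. The 1,200-patient table gives 12.7-14.3 points, depending on how the variance is split.

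**2. Model for the check.** Facility-period mean = period effect + θ_E·early + θ_L·late + facility effect + error, with facility variance ρσ² and error variance (1−ρ)σ²/n. Both θ are zero. AIC = −2 log L + 2k. Categorical period uses 3 df and a line uses 1, so AIC prefers the line when the likelihood-ratio statistic is below 2 × (3 − 1) = 4. AIC uses ML fits. The late effect is tested by a Wald z from the REML fit of the chosen model.

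**3. Check of the selection rate.** If the true trend is exactly linear, the likelihood-ratio statistic is approximately χ² on 2 df, and P(χ² < 4) = 1 − e^(−2) = 86.5%. The simulation gives 86%.

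**4. Late-effect type I error, categorical period against a straight line, ICC 0.2.** There were 20,000-60,000 replicates. At 20,000 and 8% the Monte Carlo error is √(0.08 × 0.92/20,000) ≈ 0.2 points. Ranges in the first and third rows span separate runs.

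| Assumed trend | Line chosen | Type I error |
|---|---|---|
| Flat or exactly linear | 86% | 5.5-5.7% |
| Period 2-3 dip, 0.10 SD | 47% | 7.8% |
| Period 4 step, 0.15-0.20 SD | 41-63% | 6.9-8.0% |
| Period 3 bump, 0.10-0.15 SD | – | 7.2% |
| Period 2 step, 0.20 SD | – | 6.5% |
| Period 2 dip, 0.10 SD | – | 6.0% |
| Large non-linearity, 0.3-0.4 SD | seldom | 5.1-7.2% |

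A repeat for Period 2 shapes and a large dip gave 4.9-6.3%. A search over non-linear shapes peaked at about 7.9%. At ICC 0.05 the range is 5.5-8.4%. With actual period lengths of 6, 9, 6 and 6 months it is 5.7-8.0%. Among trials in which the line is chosen, under the Period 2-3 dip or the Period 4 step, the error is about 10-12%.

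**5. Comparator.** Fixed categorical period gives 5.1-5.6% at ICC 0.2 and 5.4-6.3% at ICC 0.05. The excess over 5% comes from a Wald z test with 16 facilities, not from the time form.

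**6. Other candidate sets.** With line, quadratic and one-knot linear spline together, the maximum is about 7.0-7.2% at ICC 0.2 and 7.8% at ICC 0.05. With the one-knot linear spline as the only alternative, it is 5.0-5.5%.

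**7. Bias and price.** Under the Period 4 step the average bias is 0.024-0.029 SD. With SD = √0.2275 = 0.477, that is 1.1-1.4 points. The late-effect SE is 0.148-0.149 SD with categorical period and 0.139 with a line, a ratio of 1.06-1.07. In points: 0.149 × 47.7 = 7.1 against 0.139 × 47.7 = 6.6.

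**The case against.** The case for leaving the text alone has substance. Categorical period is the stated default, and the override was written down. The rule does not appear in the SAP analyses of treatment failure, in-care status at 15 months or missed visits. The average bias is at most 0.029/0.149 ≈ 0.2 of a standard error. The straight line is only one reading: the adjective may belong to the splines, and then a line might not be a candidate. The documents place the COVID-19 emergency in Period 2, and trends confined to Period 2 give only about 5-6.5%. All of this stands, and it limits the size of the point. It does not remove the rule, which still lets the outcome data choose the model for the main confounder without any allowance for that choice.

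Three stronger readings are tempting, and the documents support none of them.

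- A reader might infer that the TEC analysis runs at 8% error. That figure is near the worst case over assumed trends. With a flat or linear trend, selection adds under half a point.
- A reader might infer that the time form was picked after results were seen, because SAP V3.1 is dated 15 February 2022 and the TEC visit window closed on 17 November 2021. The documents do not say that anyone had seen results.
- A reader might infer that the reported late effect is an artefact. The TEC tables do not state which time form was used. The late risk difference in Table S4 is −16.9 points (−24.8 to −8.9), so SE ≈ 15.9/3.92 = 4.1 points and the estimate is about 4 standard errors from zero. This is not a re-analysis, and the binary models were not simulated, but an average bias of about a fifth of a standard error would not explain it.

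**Conclusion.** The point holds in a limited form. The SAP allows a fit statistic on the trial data to replace categorical period in the TEC model, with open candidates, no margin and no allowance for selection. If a straight line is a candidate, the late-effect type I error is about 5-8% across the trends tried, against about 5-6% with categorical period fixed. Selection adds about 2-3 points at most. The upper end needs a mild non-linear trend of 0.1-0.2 SD, such as a Period 4 step or a Period 2-3 dip. If a low-df spline is the only alternative, there is almost no inflation.

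This rests on assumed trends, on one-knot linear and quadratic stand-ins for the SAP's unspecified splines, and on the normal score model. TEC is a secondary outcome. The point is a cheap improvement and not a threat to the trial's primary conclusion.

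**What to change.** In SAP section 4.0, state that categorical period is the fixed time adjustment for all TEC outcomes, and delete the sentence that updates the model on fit. Move the linear and spline forms, with knots and degrees of freedom stated, to the Sensitivity analyses part beside ordered period and visit date. If another form has already been used for a reported TEC result, give the categorical-period estimate next to it.

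The cost is SAP wording and a late-effect standard error about 6-7% larger than under a straight line. At ICC 0.2 the late-effect detectable difference becomes 19.9 points instead of 18.6 (2.8016 × 7.1 and 2.8016 × 6.6, before rounding of the SEs). Both exceed the SAP's 15.0 because they concern the late term alone, whereas the SAP's figure was reproduced with a single intervention effect.

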#### *Analysis of individual questions from TEC survey*

We will analyze 12 dichotomous (yes/no) patient experience questions from the trained exit client (TEC) survey. Initially, binomial models with a log link (relative risk) or identity link (risk difference) will be used to analyze these data. However, it is well-known that models assuming a binomial distribution often fail to converge (Spiegelman, 2005), and if we find widespread convergence failure for either of the link functions then we will employ models that assume a Poisson distribution. If convergence issues still persist then we will also explore alternative modelling for random effects (e.g., GEE). Significant differences ( $P < 0.05$ ) with greater proportions of positive experiences in the PCC intervention group will support the hypothesis that the PCC intervention was more effective compared to the control. Results will be presented in terms of risk ratios (95% CI) and risk differences (95% CI). Forest plots with these estimates and 95% CIs will also be used to visually display the results. Additionally, we will present the absolute percentages to assess where the improvements any improvements are occurring (e.g., 40% to 50% vs 85% to 90%).

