## 2.2 Secondary outcomes

- Patient Experience from Trained Exit Client Surveys
- In Care at 15-month in care
- Missed next visit by 30 days

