#### *Analysis of PCA composite axes and survey sum scores*

The analysis for these outcomes will involve two steps. In step 1, we will estimate the tetrachoric correlations between the 12 variables from the TEC survey which will subsequently be analyzed using a principal components analysis (PCA). We will use standard methods to objectively determine the # of axes to retain and interpret including: levelling out of scree plot, eigenvalue threshold of  $> 1$ , parallel analysis, and factor loadings. If the number of axes to interpret is ambiguous, then the research team will use study specific knowledge to evaluate the results from the PCA to make decisions on which axes to include in further analysis. In step 2, we will analyze the composite scores

from the PCA analysis using the same GLMM approach as previously described with the exception that the distributional assumption will be normal with an identity link function. The estimate of interest will be the mean difference in PCA scores between the intervention and control. In addition to the PCA composite scores, we will also analyze the sum scores (i.e., the sum of the responses over all of the questions). The analytic approach will be the same for that as for the composite axes. If we find that our conclusions are similar between the two approaches (PCA and sum scores) then we will focus our interpretation on the sum scores as these provide more straightforward interpretation compared to the PCA composite scores, even though in theory PCA scores are more valid.

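### The SAP lets significant TEC items support effectiveness without saying how many of the 12 items, or which exposure contrast, must succeed, and without multiplicity control

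*Combined protocol and SAP*

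**What the plan says.** SAP section 2.2 lists "Patient Experience from Trained Exit Client Surveys" as a secondary outcome. Section 4.0 then sets out the analysis in three places.

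- **Exposure coding (Analysis).** Because a ramp-up in effect is expected, "we will determine code three different groups for the intervention analysis (control, early intervention" and late intervention, the cut being at 6 months. These are to be "fit as separate categories or ordered". The SAP does not choose between the two codings, and it does not say which contrast carries the conclusion if they are separate.
- **Item analysis (Analysis of individual questions from TEC survey).** "We will analyze 12 dichotomous (yes/no) patient experience questions from the trained exit client (TEC) survey". The criterion follows: differences significant at P<0.05 "with greater proportions of positive experiences in the PCC intervention group will support the hypothesis that the PCC intervention was more effective".
- **Composite scores (Analysis of PCA composite axes and survey sum scores).** Both are analysed. If they lead to similar conclusions, "we will focus our interpretation on the sum scores as these provide more straightforward interpretation". No success criterion is attached to either score, and the item claims do not depend on them.

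Neither the SAP nor the protocol states a multiplicity adjustment for the items, an order of testing, or an exploratory label.

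**The concern.** The item sentence is the only explicit statement in section 4.0 of what will count as evidence that the intervention improved patient experience. It can be met through 12 routes, or 24 if early and late are fitted separately. It counts only results "with greater proportions of positive experiences in the PCC intervention group", so items that move the other way carry no weight in the criterion. The outcome was sized quite differently, as one proportion with one contrast at p<0.05. A claim resting on one or two items would therefore look like a 5% test without having that error rate. Which items may be called improved would also depend on choices made after the data are seen.

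**Working it through.** **Inputs.** From the SAP: 12 items, P<0.05, favourable direction only, and one contrast per item (ordered coding, or a single contrast) or two (early and late). Taking the tests as two-sided, the favourable tail is 0.025 per test. The documents do not give the correlation between items, so a range is assumed on the test-statistic scale.

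**The plan's own figure.** No familywise rate is stated. The nearest figure is the TEC sizing: a 15.0-point difference from 65%, ICC 0.2, 80% power. A Hussey–Hughes variance for waves 2–4 (4, 4 and 8 clinics, four periods) with 15 encounters per clinic-period (protocol, Population for QIPS) and variance at 65% gives SE = 0.0524. Power = Φ(0.15/0.0524 − 1.96) = 81.7%, and the detectable difference is 2.80 × 0.0524 = 14.7 points. The figure therefore reproduces as a single unadjusted comparison. (The unequal cells of the SAP's TEC table, 1,200 patients, give 91–94%.) Nothing below depends on this.

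**Independent tests, at least one favourable result under no effect.**

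- 12 tests: 1 − 0.975^12 = 26.2%
- 24 tests: 1 − 0.975^24 = 45.5%

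**Correlated tests.** The test statistics were simulated as multivariate normal with mean zero (300,000 draws, Monte Carlo error below 0.1 point). Items are equally correlated at ρ. The early–late correlation is 0.71, taken from the stepped-wedge design matrix with the SAP's cell sizes and ICC 0.2. A result counts if Z > 1.96.

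| ρ between items | ≥1 of 12 | ≥1 of 24 | ≥2 of 12 | ≥2 of 24 |
|---|---|---|---|---|
| 0 | 26.2% | 39.7% | 3.5% | 15.1% |
| 0.3 | 20.2% | 30.2% | 6.1% | 14.3% |
| 0.5 | 16.0% | 24.1% | 6.5% | 12.8% |
| 0.7 | 11.7% | 17.8% | 6.1% | 10.7% |
| 0.9 | 6.7% | 10.6% | 4.7% | 7.7% |

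The 39.7% for 24 tests at ρ = 0 is below 45.5% because early and late share control data. A repeat of the two-of-12 case at ρ = 0.5 gave 6.6%. In the last column the two results may be the early and late contrasts of the same item.

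**Reported results.** Table S5 gives both contrasts for all 12 items, with positive differences favouring the intervention. Five of the 24 intervals exclude zero. Using z = difference ÷ (interval width/3.92):

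| Item, contrast | Difference (95% CI) | z | p |
|---|---|---|---|
| Time spent, late | 13.1 (4.3 to 21.8) | 2.93 | 0.0033 |
| Information, late | 13.8 (4.4 to 23.2) | 2.88 | 0.0040 |
| One-on-one conversation, late | 8.6 (1.7 to 15.6) | 2.43 | 0.0153 |
| Greeting, late | 7.3 (1 to 13.7) | 2.25 | 0.0242 |
| Time spent, early | 8.8 (1.0 to 16.7) | 2.20 | 0.028 |

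Holm within the 12 late contrasts: 12 × 0.0033 = 0.040, 11 × 0.0040 = 0.044, 10 × 0.0153 = 0.153. Two items survive. Holm across all 24: 24 × 0.0033 = 0.080 (unrounded p), so none survives.

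**The case against.** The SAP nowhere says that any one item, in either category, is enough. Its wording is plural, and support is a weaker word than a decision rule. If the plural is read as at least two favourable items out of 12, the false-claim rate is 3.5–6.6%, close to 5%. The coding is left open, so 24 tests is not a commitment of the plan. That both contrasts appear in Table S5 shows what was reported, not what was planned. Items about the same visit overlap in content, and at a correlation of 0.9 the rates fall to 7% and 11%. The SAP also promises forest plots, intervals and absolute percentages for all items, which would show adverse movement. Table S5 does show it: the late contrast for being shouted at or scolded is −5.8 (−13.4 to 1.8).

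Most of this stands as a limit on the claim. It does not remove the gap. The two-item rule is not written down, and with 24 tests it would still give 11–15% at correlations of 0–0.7. Choosing the ordered coding leaves 12 tests and a rate of 12–20%. Full presentation helps a reader, but it does not change what the plan says will count as support.

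**Conclusion.** The plan is silent on the number of items, the deciding contrast, multiplicity and any gate through the sum score. If one favourable item suffices, the false-support rate at item correlations of 0.3–0.7 is about 5 to 8 times the nominal 2.5% with 12 tests, and about 7 to 12 times with 24. These figures rest on the assumed correlations, on two-sided testing at 0.05, and on the one-item reading, which follows from the absence of any other rule and is not SAP text.

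A reader might infer three stronger things that the documents do not support.

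- **Error rates of 46% or 71%.** These are 1 − 0.95^12 and 1 − 0.95^24. They count results in both directions and assume independence, whereas only favourable results count as support.
- **No real effect on patient experience.** Table S4 reports a late reduction of 16.9 points (−24.8 to −8.9) in bad experiences, defined by a sum score of 8 or less. That result does not rest on any single item.
- **A threat to the trial's main conclusion.** The primary outcome is treatment failure and is untouched.

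**What to change.** In Analysis of individual questions from TEC survey, replace the sentence on support with a rule that patient experience is judged on the sum score, late intervention (>6 months) versus control. State that the 12 items are reported for both contrasts with confidence intervals as exploratory components.

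In Analysis of PCA composite axes and survey sum scores, remove the condition that the sum score leads only if the PCA scores agree, so that the deciding test is fixed regardless.

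If item-level claims are wanted, test them only after the sum-score test succeeds, with Holm across the 12 late contrasts.

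The cost is SAP wording and a Holm step in existing code. Fewer individual items can then be called significant: in Table S5, two late items in place of four. Because results already appear in the same appendix, the change should be dated and described as made after they were known. The lag in benefit that the SAP anticipates gives a reason for the late contrast that does not depend on those results.
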